The secondary research objectives are:To establish whether patients are less deeply sedated intra-operatively during patient-maintained sedation compared to anaesthetist-controlled sedation.To assess whether patients undergoing PMPS have equal reductions in peri-operative anxiety compared to patients undergoing ACPS.To observe whether patients undergoing PMPS have comparable post-operative satisfaction with their sedation experience compared to patients undergoing ACPS.To explore whether patients who have undergone PMPS are fit for discharge from the post-anaesthetic care unit (PACU) sooner than patients who have undergone ACPS.To determine if patients undergoing PMPS have calculated effect-site concentrations of propofol that are lower than in patients who undergo ACPS.To examine how many times patients using PMPS press their trigger button to increment their dose (successful button press), how many times they press the button while the device is locked out (unsuccessful button press) and whether there is a relationship between pre-operative anxiety state and use of the trigger system.To determine whether patients undergoing PMPS experience a different incidence of airway, respiratory or cardiovascular sedation-related side-effects than patients who have undergone ACPS. Airway sedation-related side-effects include partial or complete airway obstruction that requires the usual clinical anaesthetist to apply one of the following interventions: chin-lift, jaw thrust, nasopharyngeal airway insertion, oropharyngeal airway insertion, laryngeal mask insertion or endotracheal tube insertion. Respiratory sedation-related side-effects are respiratory rate fewer than 8 breaths per minute or arterial oxygen saturations less than 88% in patients with chronic obstructive pulmonary disease (COPD) or 94% in all other patients. Cardiovascular sedation-related side-effects include heart rate or blood pressure reduction greater than 20% from baseline, but such events may be related to spinal anaesthesia rather than the sedation. All such events will be noted by a study investigator and reviewed to determine the likely aetiology. There are no objective clinical criteria to determine this, but routine clinical practice is to assimilate the presented information to estimate the likely contribution from sedation, spinal anaesthesia and/or another cause.To determine whether patients undergoing PMPS experience different health-related quality of life outcomes compared to patients undergoing ACPS.

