### Enrolment

Patient screening for eligibility and recruitment will be conducted at the Theatre admission lounge, Nottingham City Hospital campus. This site is where our patients are usually treated. Screening will be performed by the supervising clinical anaesthetist during their routine pre-operative patient assessment. The supervising clinical anaesthetist will notify a study investigator of potentially eligible patients. The recruited patient will sign and date the approved version of the informed consent form before any procedures specific to the clinical investigation are performed.

The participant’s research data will be gathered during a single visit to hospital, which forms part of usual clinical care. A telephone consultation between a study investigator and each participant will be performed at post-operative day 7–10.

After enrolment, the participant will be given a group-specific laminated educational leaflet explaining their sedation system. Those allocated to PMPS will receive written instructions on the use of the PMPSD and those allocated to ACPS will receive written explanation on how their supervising clinical anaesthetist will sedate them.

A pre-operative questionnaire will be administered to all participants before they are taken to the anaesthetic room. The following data will be recorded: age, gender, whether hip or knee arthroplasty, surgeon initials, supervising clinical anaesthetist initials, patient weight and height, American Society of Anaesthetist Physical Status Classification, respiratory rate, arterial oxygen saturations, heart rate, blood pressure (systolic, diastolic, mean) and sedation score on the Modified Observer’s Assessment of Alertness/Sedation (mOAA/S) Scale.

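### The oxygen-saturation side-effect is defined by an absolute cut-off with no reference to baseline, so a participant already below it at entry meets the definition without any change under sedation

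*Protocol article*

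**What the plan says.** The secondary objective on side-effects (protocol article, Study objectives) covers three domains. For the respiratory domain it states: "Respiratory sedation-related side-effects are respiratory rate fewer than 8 breaths per minute or arterial oxygen saturations less than 88"; the full saturation clause is "arterial oxygen saturations less than 88% in patients with chronic obstructive pulmonary disease (COPD) or 94% in all other patients". The next sentence takes a different approach for the circulation: "Cardiovascular sedation-related side-effects include heart rate or blood pressure reduction greater than 20% from baseline". After a remark that such events may come from the spinal anaesthetic, the text adds: "All such events will be noted by a study investigator and reviewed to determine the likely aetiology". It concedes that objective criteria for this do not exist, and says that clinicians will weigh the information to "estimate the likely contribution from sedation, spinal anaesthesia and/or another cause".

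The Inclusion criteria and Exclusion criteria contain no saturation or lung-disease limit. Under Enrolment, the pre-operative data include "American Society of Anaesthetist Physical Status Classification, respiratory rate, arterial oxygen saturations, heart rate, blood pressure", so each participant has a baseline saturation. Under Safety, saturation is then recorded every 5 minutes during sedation in both arms.

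**The concern.** The outcome is labelled sedation-related, but its saturation component tests only a level. Someone without COPD who arrives just under 94%, or someone with COPD who arrives just under 88%, satisfies it if their saturation stays where it was. The design can enrol such people, and the 88% clause shows that participants with lower resting saturations were expected. The adjacent cardiovascular rule uses baseline, and the value needed to do the same here is already on the form.

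Collecting safety data on a prototype device is a stated purpose of the trial (Abstract, Background). If low saturation at entry is counted, the reported incidence mixes pre-existing findings with new ones, and the difference between patient-maintained and anaesthetist-controlled sedation is harder to see.

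**Working it through.** **The plan's own figures.** The article gives no expected rate for respiratory side-effects. Its only calculation is for the primary outcome, and it reproduces. With means 1.580 and 2.231 (difference 0.651), SDs 0.755 and 0.915 and a two-sided 5% level, Welch power from the noncentral t distribution is 89.2% at 35 per arm and 90.07% at 36 per arm. That gives 72 in total, and 72/0.9 = 80 after drop-out. The present point does not touch this. It supplies only the arm size of 40 used below.

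**The rules side by side.**

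| Component | Form of the rule | Uses baseline? |
|---|---|---|
| Respiratory rate | below 8 per minute | no |
| Saturation | below 88% (COPD) or 94% (others) | no |
| Heart rate, blood pressure | fall of more than 20% | yes |

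**Effect on the incidence.** Let q be the share of participants below their own cut-off at entry, p the true rate of new events in the rest, and suppose that everyone low at entry is counted.

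- Observed rate = q + (1-q)p
- Observed risk difference = [q + (1-q)p2] - [q + (1-q)p1] = (1-q)(p2-p1)
- Expected number low at entry per arm = 40q

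Neither q nor p is in the documents. All values below are assumptions: p1 = 10%, p2 = 30%, and q over a range.

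| q | Low at entry per arm | Observed rates | Risk difference | Risk ratio |
|---|---|---|---|---|
| 0 | 0 | 10% vs 30% | 20 points | 3.0 |
| 3% | 1.2 | 12.7% vs 32.1% | 19.4 points | 2.5 |
| 10% | 4 | 19% vs 37% | 18 points | 1.9 |
| 15% | 6 | 23.5% vs 40.5% | 17 points | 1.7 |

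Example at q = 10%: 0.10 + 0.90 × 0.10 = 0.19 and 0.10 + 0.90 × 0.30 = 0.37. The difference is 0.18 and the ratio 0.37/0.19 = 1.9.

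**Effect on precision.** The approximate power of a two-sided 5% comparison of two proportions with n per arm is Φ{[d - 1.96√(2p̄(1-p̄)/n)] / √[(pa(1-pa) + pb(1-pb))/n]}. Here pa and pb are the observed rates, d is their difference and p̄ is their mean. At n = 40 it is 61% for q = 0, 55% for q = 3% and 43% for q = 10%. The trial was not sized for this comparison, so these figures only show direction and scale.

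**After the change.** If only those at or above the cut-off at entry are counted, the rates return to 10% and 30% with 40(1-q) per arm. At q = 10% that is 36 per arm, and power is Φ[(0.20 - 1.96 × 0.0943)/0.0913] = Φ(0.166), about 57% instead of 43%.

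**The case against.** The strongest reply is that the aetiology review already deals with this. It allows for causes other than sedation, and the reviewer can see the baseline saturation. That may be so, and for this reason a reader should not infer that pre-existing low saturation will end up attributed to sedation. The text shows only that it meets the definition. The review is not a full answer, however. Its sentence follows the cardiovascular definition and most naturally refers to those events. It works, by its own account, without objective criteria, and the article does not say that events attributed elsewhere leave the count.

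A second reply is that an absolute level is a legitimate safety definition, consistent with the respiratory-rate rule, and that dropping people who are low at entry could hide a serious fall in a vulnerable participant. This stands, and the fix has to keep those participants visible.

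Three stronger readings are tempting but unsupported:

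- **COPD status is not collected, or is decided by an unblinded investigator after allocation.** It is absent from the list under Enrolment, but an article condenses the case report form. The supervising anaesthetist's pre-operative assessment comes before consent, and the envelope stays closed until consent is given.
- **The comparison is biased towards one arm.** Randomisation makes q equal in expectation. Chance imbalance in a few participants is possible, as for any baseline factor.
- **The first 5-minute reading precedes any propofol effect.** Nothing in the article shows this, nor does it say whether a low pre-operative reading persists into theatre.

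The BMI limits are also no evidence of low saturation. The article gives them solely for the lean-body-mass formula in the infusion model.

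**Conclusion.** The point holds as a minor defect in the definition of one component of one secondary objective. As written, a participant below the cut-off at entry satisfies the saturation criterion without deteriorating, although the baseline value that would separate old from new is already recorded.

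The consequence is a raised incidence in both arms and a modest dilution of the contrast. The risk difference is multiplied by 1-q, so an assumed 20 points falls to between 19.4 and 17 points for q from 3% to 15%. The risk ratio looks worse (3.0 down to 1.7) because the same background is added to both rates. These sizes rest on assumed rates, on everyone low at entry being counted, and on q being equal in the arms. If q is close to zero, the effect is negligible. The primary outcome and the sample size are not affected.

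**What to change.** Keep the existing cut-offs and change how events are counted:

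1. Count a saturation event as sedation-related only when the participant's recorded pre-operative saturation was at or above that participant's cut-off.
2. Report participants below the cut-off at entry separately, by change from baseline.
3. Give the unrestricted count, under the present definition, next to the restricted one, so that no desaturation is hidden.
4. Assign the 88% or 94% cut-off from COPD status as known at the pre-operative assessment, before the envelope is opened.
5. State whether the aetiology review applies to respiratory events.

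The cost is a few sentences in the outcome definition and one extra line in the safety table. Baseline saturation is already collected. The small downside is that the few participants below the cut-off at entry leave the main binary count, which items 2 and 3 offset.

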### Study objectives

The primary research objective is to compare the body-weight-normalised rate of propofol consumption when sedation for surgery on adults undergoing elective primary lower-limb arthroplasty under spinal anaesthesia (effect-site-targeted with propofol) is patient-maintained versus when it is anaesthetist-controlled. The primary outcome will be expressed as milligrams propofol per kilogram actual body weight per hour of the sedation period. The sedation period is defined as the time from commencement of the allocated sedation regimen by the supervising clinical anaesthetist (which will be after spinal blockade is confirmed by clinical dermatomal testing) until the sedation regimen is discontinued at the end of surgery (which will be at the application by the operating surgeon of clips to skin).

The study primary null hypothesis is that there is no difference in the rate of propofol consumption when sedation it is patient-maintained versus anaesthetist-controlled. The primary alternative hypothesis is that a patient-maintained propofol sedation regimen will result in a minimum 29% reduction in the rate at which propofol is consumed over the course of the sedation period compared to anaesthetist-controlled propofol sedation.

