### Safety

All pre-existing medication taken by a participant as part of their usual medical care will be permitted. Co-administration of sedatives, hypnotics or analgesics during placement of spinal anaesthesia or during the intra-operative sedation regime at the discretion of the supervising clinical anaesthetist will be recorded. Behavioural disinhibition is a well-recognised side-effect of propofol sedation. This occurs regardless of whether the propofol is delivered by intermittent bolus, fixed rate infusion or target-controlled infusion. It manifests as patient movement (usually of the upper limbs) and/or talking. It does not always respond readily to simple verbal command from the supervising clinician to desist. The standard treatment for this is for the supervising clinical anaesthetist to actively alter the depth of sedation at their discretion by either lightening or deepening the degree of sedation according to clinical circumstances and their professional judgement. In either arm of the trial, if a patient displays disinhibited behaviour that is disruptive to surgery or potentially dangerous for the patient (for example, risking pulling out their intravenous cannula), the supervising clinical anaesthetist will be free to alter the patient’s depth of sedation either by lightening or deepening sedation, using a sedative agent of their discretion. This will be recorded. No medications will be specifically prohibited in this trial.

In order to detect physiological changes that may suggest unsafe sedation, both trial arms will have heart rate, respiratory rate, arterial oxygen saturations, blood pressure and depth of sedation measured and recorded at 5 min intervals throughout the sedation period. Adverse events, adverse device events, serious adverse events and serious adverse device events will be recorded and reported to the relevant bodies (trial Sponsor, device manufacturer, Research Ethics Committee, Medicine and Healthcare products Regulatory Agency).

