### Intervention

The usual clinical care of non-invasive physiological monitoring will be established by the supervising clinical anaesthetist. They will insert an intravenous cannula and spinal anaesthesia will be performed. When satisfied that adequate spinal anaesthesia has been accomplished, they will commence the participant on their allocated sedation regime.

Participants allocated to PMPS will have their sedation infusion commenced at the minimum level of 0.5 μg.mL^− 1^ and will be given the handheld trigger button to press. They will be told *“*Press the button if you want to be more sleepy*”*. Participants allocated to ACPS will be commenced on an effect-site-steered TCI propofol infusion. The supervising clinical anaesthetist will control the effect-site target at their discretion.

Both sedation regimes will commence in the anaesthetic room, prior to the participant moving to theatre. A study investigator will record physiological and sedation outcome measures at 5-min intervals throughout the sedation period.

The sedation regime will be discontinued at the end of surgery when skin clips are applied to the wound. This time will be noted by a study investigator. In the PMPS group the handheld button will be withdrawn from the patient and the TCI infusion stopped. In the ACPS group the TCI infusion will be stopped. If, for any reason, the sedation is discontinued prior to end of surgery, the reason will be noted in a free-text narrative response by a study investigator.

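### Cardiovascular side-effects are classed as sedation-related by judgement without criteria in an open-label trial, and the baseline for the 20% fall is not dated; compare all falls by arm instead

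*Protocol article*

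**What the plan says.** Under Study objectives, the protocol article asks whether patients on patient-maintained sedation (PMPS) "experience a different incidence of airway, respiratory or cardiovascular sedation-related side-effects than patients who have undergone ACPS", where ACPS is the anaesthetist-controlled arm. The cardiovascular component is "heart rate or blood pressure reduction greater than 20% from baseline, but such events may be related to spinal anaesthesia rather than the sedation". A study investigator notes every such event, and each is reviewed for its probable cause. On that review the article says: "There are no objective clinical criteria to determine this". Routine clinical judgement is to estimate how much is owed to sedation, the spinal or something else.

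The article does not say when baseline is taken, or which blood pressure (systolic, diastolic or mean) the 20% applies to. Four other statements bear on it:

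- Enrolment: "A pre-operative questionnaire will be administered to all participants before they are taken to the anaesthetic room". Heart rate and blood pressure are among the data listed there, but are not called baseline.
- Intervention: "When satisfied that adequate spinal anaesthesia has been accomplished, they will commence the participant on their allocated sedation regime".
- Study objectives, on the start of sedation: "which will be after spinal blockade is confirmed by clinical dermatomal testing".
- Safety: heart rate and blood pressure are "measured and recorded at 5 min intervals throughout the sedation period".

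Under Trial blinding, the Discussion says that the investigator collecting intra-operative data is not blinded. It does not say who reviews cause, or whether that person is masked.

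**The concern.** The outcome is named for sedation, but its numerical definition cannot tell a sedation effect from a spinal effect. The article concedes this and relies on case-by-case judgement to separate the two. If the compared incidence is the number of events judged sedation-related, the arm difference depends on two things: how often pressure or heart rate fell, and how readily a fall was blamed on sedation. The second can differ between arms when the person judging knows the allocation and has no written rule. Randomisation balances the patients, not the judgement.

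The undated baseline is a second and lesser problem. If the reference is a reading taken before the spinal, falls caused by the spinal enter the count in both arms and make any real sedation difference harder to see.

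At stake is one component of one secondary objective. It matters because the trial is also meant to gather safety data on a prototype device. A difference created by attribution, or a real one lost in spinal events, could be misread as evidence on the device's safety.

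**Working it through.** **Inputs from the article.** Two equal arms; two-sided 5% level; 80 participants, hence 80/2 = 40 per arm at most. The article's only calculated figure is the primary-outcome sample size, and it reproduces. With means 1.580 and 2.231 and SDs 0.755 and 0.915, Welch's test has power 0.892 at 35 per arm and 0.901 at 36. That gives 72 in total, and 72/0.90 = 80. No sample size, power or event rate is given for the cardiovascular outcome, so all event rates below are assumptions.

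**Step 1: attribution bias.** Let E be the all-cause event rate, equal in both arms, so there is no true difference. Let q be the share of events ascribed to sedation. The observed sedation-related rate is E × q.

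- E = 0.60, q = 0.60 (ACPS) and 0.40 (PMPS): 0.60 × 0.60 = 0.36 and 0.60 × 0.40 = 0.24.
- Probability of a significant result, pooled z-test with n = 40 per arm: Φ[(d − 1.96 × √(2p̄(1−p̄)/n)) / √((p₁(1−p₁) + p₂(1−p₂))/n)].
- Here d = 0.12 and p̄ = 0.30. The standard errors are √(2 × 0.30 × 0.70/40) = 0.1025 and √((0.2304 + 0.1824)/40) = 0.1016.
- Φ[(0.12 − 0.2008)/0.1016] = Φ(−0.796) = 0.21. Exact enumeration over all pairs of binomial counts also gives 0.21. With equal attribution (0.30 v 0.30) it gives 0.048, close to the nominal 0.05.

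Over a range of assumptions (normal approximation):

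| All-cause rate, both arms | Shares ascribed, ACPS / PMPS | Observed rates | P(significant) |
|---|---|---|---|
| 40% | 60 / 40 | 24% v 16% | 0.14 |
| 40% | 70 / 30 | 28% v 12% | 0.43 |
| 60% | 60 / 40 | 36% v 24% | 0.21 |
| 60% | 70 / 30 | 42% v 18% | 0.65 |
| 80% | 60 / 40 | 48% v 32% | 0.31 |
| 80% | 70 / 30 | 56% v 24% | 0.85 |

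The direction shown is arbitrary. Swapping the shares gives the same probabilities against the device.

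**Step 2: which baseline the text implies.** In time order, the article describes the pre-operative record, then transfer to the anaesthetic room, the spinal, confirmation of the block, the start of sedation and 5-minute readings. The only heart rate and blood pressure described before sedation is therefore the pre-operative one, taken before the spinal. That makes it the likeliest baseline, but by inference only. A reading at the moment sedation starts is neither stated nor ruled out.

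**Step 3: dilution if baseline is pre-spinal.** Let s be the chance that the spinal alone causes an event, equal in both arms, and a the chance that sedation does, independently. Then observed risk = 1 − (1 − s)(1 − a). Assume a = 0.30 (ACPS) and 0.10 (PMPS). For s = 0.4: 1 − 0.6 × 0.7 = 0.58 and 1 − 0.6 × 0.9 = 0.46.

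| s | Observed rates | Risk ratio | Power, 40 per arm (exact) |
|---|---|---|---|
| 0 | 30% v 10% | 3.0 | 0.63 |
| 0.2 | 44% v 28% | 1.57 | 0.32 |
| 0.4 | 58% v 46% | 1.26 | 0.20 |
| 0.6 | 72% v 64% | 1.13 | 0.12 |

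This is loss of power, not bias: with equal a in the two arms the observed rates are equal for any s. Even at s = 0 the power for an assumed threefold risk is only 0.63.

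Steps 1 and 3 describe alternatives. Step 1 applies if the attributed count is compared, and step 3 if every fall is counted. They should not be added together.

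**The case against.** The article discloses both the spinal confounding and the lack of criteria. It says all such events are noted, so an all-cause count by arm can be produced. Randomisation balances spinal events in expectation. A condensed article may leave the baseline time point to the full protocol, and the schedule figure is not shown here. The reviewer of cause may be masked. A start-of-sedation baseline is not clearly better: the 5-minute schedule does not guarantee a reading before propofol flows, a dermatomal test does not show that the haemodynamic effect of the block is complete, and a patient already hypotensive has less room to fall.

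Most of this stands, and it limits the point in three ways. First, a reader might infer that baseline is fixed before the spinal; the article does not say so. Second, a reader might infer that spinal hypotension swamps the comparison. That would need a spinal event rate, which the article does not give, and the effect would be dilution rather than bias. Third, a reader might infer that cause is judged unblinded. That is stated only for the investigator collecting intra-operative data, and masking of the review is left open.

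Disclosure does not answer the attribution problem. The stated objective compares events called sedation-related, the stated means of identifying them is judgement without criteria, and nothing in the text protects that judgement from knowledge of the arm. Noting all events makes the remedy possible but does not make the all-event count the comparison.

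**Conclusion.** The concern holds for attribution. As written, the comparison is open to differential attribution between arms, which randomisation does not remove. On the assumed figures, no true difference could appear as 36% v 24%, significant about 21% of the time instead of 5%; over the range tried, the probability runs from 0.14 to 0.85. These figures rest on assumed event rates, assumed attribution shares, 40 analysed per arm and an uncorrected 5% test. They show what could happen, not what will.

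The baseline point holds only as a missing time point. If the pre-operative reading is meant, dilution follows, and its size cannot be known from the article.

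The primary outcome, the sample size of 80 and the airway and respiratory definitions are unaffected. This is a cheap improvement to one secondary safety outcome.

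**What to change.** - Make the between-arm cardiovascular comparison on all falls of more than 20% during the sedation period, whatever the attributed cause.
- Report the investigator's view of cause by arm as descriptive only.
- State the time point of baseline and which blood pressure measure is used.
- Show the count from the pre-operative value and, beside it, the same count from a reading taken at the start of the sedation regimen, after the block is confirmed.

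Cost: a few sentences, one extra table and, if it is not already taken, one reading fixed at the start of sedation. The start-of-sedation version leaves less room for a further fall and may still contain some evolving spinal effect. The pre-operative version contains the spinal effect in full. Neither is clean, so both should be shown and neither should replace the other.
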